## Abstract

**Introduction:**

Midfoot osteoarthritis (OA) is a painful and disabling condition. Arch contouring foot orthoses have been recommended for midfoot OA, yet there is no high‐quality evidence from randomised controlled trials to support their use. This clinical trial aims to evaluate the efficacy of arch contouring foot orthoses for midfoot OA.

**Methods:**

This will be a parallel‐group randomised controlled superiority trial. One‐hundred and forty community‐dwelling people with painful midfoot OA will be randomised to receive either arch contouring foot orthoses or flat sham inserts. Outcome measures will be obtained at baseline, 4, 8 and 12 weeks; the primary endpoint for assessing efficacy being 12 weeks. The primary outcome measure will be average midfoot pain whilst walking over the last 7 days on an 11‐point numerical rating scale. Secondary outcome measures include function (walking/standing subscale of the Manchester–Oxford Foot Questionnaire), participants' perception of overall treatment effect (self‐reported global rating of change on a 15‐point Likert scale), physical activity (Incidental and Planned Exercise Questionnaire), general health‐related quality of life (Short Form‐12 Version® 2.0), use of co‐interventions and adverse events.

**Discussion:**

This trial will evaluate the efficacy of arch contouring foot orthoses for relieving pain and improving function, physical activity and health‐related quality of life in people with midfoot OA. The findings will provide high‐quality evidence as to whether arch contouring foot orthoses are efficacious and will help to inform clinical guidelines about the use of foot orthoses for midfoot OA.

**Trial registration:**

Australian and New Zealand Clinical Trial Registry (ACTRN12623000953639).

## INTRODUCTION

1

Midfoot osteoarthritis (OA) is a common and painful condition that affects 1 in 8 adults over the age of 50 [1]. The midfoot is made up of several articulations including the tarsometatarsal joints (first, second and third cuneo‐metatarsal joints [CMJs] and fourth and fifth cuboid‐metatarsal joints), the navicular‐first, ‐second and ‐third cuneiform joints (N1CJ, N2CJ and N3CJ), the talonavicular joint (TNJ) and the calcaneocuboid joint [2, 3, 4, 5, 6]. Although midfoot OA is often described as dorsal midfoot pain aggravated by weight‐bearing activities [7], there is no universally agreed definition or diagnostic criteria for this condition [4, 8, 9]. Midfoot OA typically affects more than one joint, and three phenotypes have been reported based on the pattern of joint involvement observed in radiographs: the medial midfoot (TNJ, N1CJ or first CMJ), the central midfoot (second CMJ) or both the medial and central midfoot joints [4]. Midfoot OA is the most disabling type of foot OA [3] and significantly impacts both physical and mental health‐related quality of life [10, 11]. People with midfoot OA experience physical impairments, including reduced foot and leg muscle strength [12], and have limitations in activities, such as walking and climbing stairs [13, 14], with over 80% reporting the condition to be disabling [14]. In addition, they report increased levels of anxiety and depression [13, 14]. The aetiology of midfoot OA is multi‐factorial and not completely understood. However, several factors are associated with the condition including older age, female sex, manual occupations, obesity, pain in other weight‐bearing joints, previous foot and ankle injury, and having other non‐musculoskeletal comorbidities [14].

Altered foot and lower limb biomechanics are also associated with midfoot OA [4, 13, 15, 16, 17]. A systematic review found that people with midfoot OA have a flatter foot posture, longer central metatarsals, greater first ray mobility, reduced range of motion in the subtalar and first metatarsophalangeal joints as well as increased peak plantar pressures, pressure time integrals and contact times in the heel and midfoot while walking [15]. These variations are hypothesised to create increased mechanical stress within the midfoot, which may contribute to the development of midfoot OA. These findings are supported by investigations using magnetic resonance imaging (MRI), which have identified patterns of bone marrow lesions, an indicator of bone stress, in the midfoot region of people with symptomatic midfoot OA [18]. Furthermore, biomechanical studies have shown an association between increased medial plantar loading of the foot with pain and disability in people with midfoot OA [13, 16].

Despite the burden of foot OA, there are no clinical guidelines for the management of midfoot OA [10, 19]. Several interventions have been recommended for the initial management of midfoot OA, including arch contouring foot orthoses [20, 21], but there is uncertainty regarding their clinical effectiveness [22]. One biomechanical study reported that arch contouring foot orthoses decreased hindfoot and forefoot maximum force and peak pressure, and increased maximum force and contact area under the midfoot [23]. These effects have been theorised to be beneficial by reducing bending moments across the midfoot joints, reducing medial longitudinal arch deformation and midfoot joint compression [16, 20, 23]. Despite this mechanistic reasoning, only two studies [20, 21] have evaluated the efficacy of arch contouring foot orthoses for midfoot OA. In a case series of 57 participants [21], the use of custom‐made arch contouring foot orthoses (made of dual‐density ethylene vinyl acetate) was associated with improved pain and function for up to 6 months. More recently, a feasibility randomised controlled trial [20] of 37 participants demonstrated improvements in foot pain and foot‐related disability with the use of prefabricated arch contouring foot orthoses (VectOrthotic® devices made of a three‐quarter composite polypropylene with a 4 mm compressed closed cell polyethylene top cover) when compared to flat inserts (4 mm compressed closed cell polyethylene) at 12 weeks. Although these findings are promising, there remains uncertainty regarding the effectiveness of arch contouring foot orthoses for midfoot OA as these studies either lacked a control group [21] or were insufficiently powered to statistically detect clinically important findings [20].

Accordingly, high‐quality randomised controlled trials that are adequately powered to detect clinically important findings are now needed. Therefore, the aim of this trial is to evaluate the efficacy of foot orthoses for midfoot OA.

## MATERIALS AND METHODS

2

### Study design

2.1

The *F*oot *O*rthoses for *M*idfoot *O*A (FOMO) trial will be a parallel‐group, participant‐ and assessor‐blinded, randomised controlled superiority trial over 12 weeks. The study has been registered with the Australian and New Zealand Clinical Trials Registry (ACTRN12623000953639). This study protocol has been reported using the Standard Protocol Items: Recommendations for Interventional Trials (SPIRIT) guidelines [24], and the associated checklist from the 2022 extension of the SPIRIT 2013 statement [25] is included as Additional file 1.

### Ethical approval

2.2

Ethical approval has been obtained from the La Trobe University Human Research Ethics Committee (reference number: HEC23237). All participants will provide informed consent prior to being recruited into the trial.

### Participants

2.3

One hundred and forty participants will be recruited. To be eligible for inclusion, participants must: (i) be aged ≥18 years, (ii) have pain in the midfoot joints (located in at least one area in a predetermined dorsal midfoot region [26]) for at least 3 months that is aggravated by weight‐bearing activities, (iii) have pain in the midfoot when walking during the last 7 days that is rated an average of at least 3 out of 10 in severity on an 11‐point numerical rating scale (NRS) (where 0 represents ‘no pain’ and 10 represents the ‘worst pain imaginable’), (iv) have radiographic evidence of midfoot OA (defined in this trial as a minimum score of 1 for either observations of joint space narrowing or osteophytes in at least one of the midfoot joints in either radiographic view) assessed using the La Trobe University Atlas of Foot OA [27], (v) be able to walk household distances (more than 50 m) without the aid of a walker, crutches or cane, (vi) be willing to regularly wear shoes that will accommodate shoe inserts, and (vii) be willing to attempt to not use co‐interventions (including pain relieving oral medications) during the study period.

Participants will not be eligible for inclusion if they: (i) have had previous ipsilateral foot surgery or are planning surgery in the next 12 weeks, (ii) have OA secondary to other issues such as major trauma, (iii) have the presence of other foot or ankle condition(s) or have pain in another location that is greater than the pain in the midfoot, (iv) have any musculoskeletal or systemic medical conditions (e.g. suspected inflammatory joint disease or neurological conditions) that could make them unsuitable for inclusion or confound pain and functional assessments of the midfoot, (v) are unable to speak and read English, (vi) have had treatment that includes the use of any foot orthoses (including shock absorption shoe inserts), ankle braces and/or, received intra‐articular injections at the midfoot in the previous 12 weeks, and (vii) have dementia or any cognitive impairment.

### Recruitment

2.4

Participants will be recruited using the following methods: (i) postal invitation using a database of patients from the La Trobe University Health Sciences Clinic, (ii) social media advertising, (iii) posters placed in the local community, (iii) mail‐out and/or online advertisements to healthcare practitioners in the local area, and (iv) provision of information flyers at orthopaedic triage clinics in hospitals around Melbourne, Australia.

### Baseline assessments

2.5

Participant characteristics (such as age, gender, sex, country of birth, ethnicity, education, major medical conditions, medications and foot pain duration) will be obtained upon enrolment via an online questionnaire designed in a secure web platform (REDCap™, Research Electronic Data Capture, Vanderbilt University, USA). The following anthropometric measurements and clinical assessments will be conducted in person: (i) height and weight will be measured using a digital scale and body mass index will be calculated as weight (kg)/height (m^2^), (ii) foot pain and location will be determined by clinical assessments, such as palpation and passive range of motion testing [28], and self‐reported using a standardised foot manikin diagram (^©^The University of Manchester 2000. All rights reserved) [26], (iii) static foot posture will be assessed using the Foot Posture Index [29], (iv) foot and ankle range of motion will be measured based on previously published, reliable protocols [30, 31], (v) foot and ankle muscle strength will be measured with a CITEC hand‐held dynamometer (CIT Technics, The Netherlands) using a previously documented, reliable protocol [32], and (vi) footwear will be assessed using selected items from the Footwear Assessment Tool [33].

### Radiographic assessment

2.6

Participants will be required to undergo radiographic imaging (weight‐bearing radiographs in dorso‐plantar, lateral and oblique projections) of their symptomatic foot (or most symptomatic foot). The severity of radiographic midfoot OA will be evaluated using the La Trobe University Atlas of Foot OA [27]. The radiographs will be assessed by experienced investigators ([name] and [name]) with agreement by consensus. Radiographic evidence of midfoot OA will be defined as having a score of at least 1 for either the presence of joint space narrowing or osteophytes in any of these midfoot joints (first and second CMJ, N1CJ, or the TNJ) from any of the radiographic projections.

### Randomisation

2.7

Participants will be randomised to either the arch contouring foot orthoses or the sham inserts in a 1:1 ratio with random permuted block sizes of 4 and 6 using an online randomisation service (www.sealedenvelope.com). An independent person who is not involved in the study design, recruitment or data analysis will create and upload the allocation sequence to REDCap™. The randomisation feature in REDCap™ facilitates allocation concealment by having different user rights. To prevent subversion of the allocation sequence, none of the assessors involved in recruitment and data collection will have user rights to access the uploaded allocation sequence. All baseline assessments will be completed prior to group allocation.

### Blinding

2.8

Participants will be blinded to group allocation by limited disclosure. Participants will be advised that the clinical trial has been designed to compare one of two types of shoe inserts for midfoot OA, but they will not be informed about the specific characteristics of the interventions. Due to the nature of the intervention (i.e. foot orthoses), research staff administering them cannot be blinded. The interventions will be referred to as ‘shoe inserts’ throughout the study and both groups will receive the same clinical guideline‐based information and support at the start of the trial. Primary and secondary outcomes are participant‐reported, thus this trial will also be considered assessor‐blinded (as participants are blinded). Trial personnel entering participant‐reported data and the biostatistician performing the statistical analyses for the trial will be blinded.

### Study procedure

2.9

Participant flow through the trial is outlined in Figure 1. All face‐to‐face assessments will be performed in the Foot and Ankle Laboratory at La Trobe University and/or the La Trobe University Health Sciences Clinic in Melbourne, Victoria, Australia. Online questionnaires via REDCap™ will be sent every 4 weeks, with the final follow‐up questionnaire at 12 weeks. Table 1 shows the schedule of enrolment, interventions that will be used and the outcome measures for this trial according to the SPIRIT recommendations [24, 25].

**FIGURE 1 jfa270000-fig-0001:**
[figure not shown]
Participant flow through the trial.

**TABLE 1 jfa270000-tbl-0001:** SPIRIT diagram of enrolment, interventions and assessment for the FOMO trial.

[figure not shown]

Abbreviations: FOMO, *F*oot *O*rthoses for *M*idfoot *O*steoarthritis; SPIRIT, Standard Protocol Items: Recommendations for Interventional Trials; −*t*
_1_, enrolment (clinic); *t*
_0_, allocation (clinic); *t*
_1_, week 4 (online); *t*
_2_, 8 week (online); *t*
_3_, week 12 (online or in clinic).

### Interventions

2.10

#### Intervention group

2.10.1

Participants in the intervention group will be provided with two pairs of full‐length prefabricated arch contouring foot orthoses (Formthotics™; 140 kg/m^3^ single‐density closed‐cell polyurethane foam, Foot Science International, New Zealand) (Figure 2). The foot orthoses will be fitted into the shoes that they wear most regularly by a registered podiatrist and will be modified with the addition of a 4° medium density varus wedge if the foot posture index is >7 [29, 34, 35]. As recommended by the manufacturer, the orthoses will then be heated and placed in the participant's footwear. The participant will be required to stand in their footwear with the heated foot orthoses to facilitate custom moulding to the plantar surface of the foot and medial longitudinal arch. This is the recommended standard clinical care using this intervention. The decision to use this intervention is based on our recent survey on the current practices of Australian podiatrists for the management of midfoot OA (manuscript in preparation).

**FIGURE 2 jfa270000-fig-0002:**
[figure not shown]
Intervention.

#### Control group

2.10.2

Participants in the control group will be provided with two pairs of full‐length sham inserts made from 3 mm prefabricated flat inserts (140 kg/m^3^ single‐density, closed‐cell polyurethane foam, Foot Science International, New Zealand). The sham inserts will be the same colour and have the same branding as the foot orthoses used in the intervention group but without the heel and arch support (Figure 3). This type of device is considered a credible ‘sham’, based on previous randomised trials [35, 36] that found no difference in participants' perceptions of the *credibility* of flat sham inserts and arch contouring foot orthoses, using the Credibility/Expectancy Questionnaire (CEQ) [35] and the Treatment Credibility Scale [36]. The flat sham inserts will be fitted into the shoes they wear most regularly by a registered podiatrist.

**FIGURE 3 jfa270000-fig-0003:**
[figure not shown]
Control.

The provider of the foot orthoses and sham inserts (Foot Science International, New Zealand) will have no input into the design or implementation of the trial. They will not participate in data analysis, interpretation of the data generated from the trial, manuscript preparation or dissemination of the trial findings.

#### Clinical guideline‐based information and support

2.10.3

Participants in both groups will receive a standardised education package derived from clinical guidelines for management of OA [37, 38] and our recent survey on the current practices of Australian podiatrists for the management of midfoot OA (manuscript in preparation). Education will include guidance regarding midfoot OA (i.e. information on epidemiology, location of affected joints and associated factors), OA flares, advice relating to exercise such as activity modification, weight loss, the use of topical non‐steroidal anti‐inflammatory drugs (NSAIDs) and footwear.

Participants in both groups will be advised to use their allocated shoe inserts in their footwear for as much time as they can during the day for the 12 weeks of the trial. Insole wear will be monitored by recording the average days per week, plus the average number of hours per day the participant has worn the arch contouring foot orthoses or sham inserts, assessed via online questionnaires at each 4‐weekly timepoint. Participants will be requested to attempt to not use co‐interventions (including pain relieving oral medications) during the study, but if they do, they are required to document the use of co‐interventions in the 4‐weekly online questionnaires.

### Treatment credibility/expectation

2.11

Treatment credibility (participants' beliefs about the logic underpinning the intervention) and treatment expectancy (participants' perceptions of how much they may benefit) will be measured using the CEQ [39]. The CEQ will be administered after allocation. The CEQ consists of six items; three are related to credibility and three are related to expectancy. For each item, participants will be asked to rate the credibility of the intervention and their expectations on a 9‐point Likert scale. High scores on the scale indicate that the participant considers the intervention to be credible and expects it to be effective.

### Outcome measures

2.12

The primary outcome will be measured prior to allocation at baseline and at 12 weeks (the primary endpoint). All secondary outcomes unless stated otherwise will be measured prior to allocation at baseline and at 4, 8 and 12 weeks. Participants will complete online questionnaires at 4 week intervals, and they will be encouraged to contact the researchers at any time during the trial if needed. The outcome measures and associated timepoints are shown in Table 1.

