### Sample size

2.19

An a priori sample size calculation was conducted using G*Power version 3.1.9.7 [56, 57]. Using an allocation ratio of 1:1, power of 80%, assuming a minimal clinically important difference of 1.1 points [20] (representing a medium effect size [Cohen's *d*] of 0.5), standard deviation of 2.2 points [20], alpha set at 0.05 and allowing a 10% participant loss to follow‐up [20], a sample size of at least 140 participants (i.e. approximately 70 per group) will be required.

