### Statistical analysis

2.20

Statistical analysis will be performed using the most recent version of SPSS available to the researchers using the intention‐to‐treat principle for all randomised participants. In participants with bilateral symptoms, the more painful side will be analysed (or the right lower limb if they cannot decide which is the more painful side) to maintain independence of data [58]. Standard tests to assess continuous data for normal distribution will be used. If continuous data is not normally distributed, transformation will be carried out if appropriate. Multiple imputation will be used to replace any missing data using five iterations, with sex, age, baseline scores and group allocation as predictors [59]. The exception will be for the GROC scale, co‐interventions, adherence and adverse events where no data substitution will be applied.

The primary outcome measure will be NRS pain measured at 12 weeks. To avoid over‐testing and to minimise the risk of type I error associated with serial measurements, statistical analysis of the efficacy of the interventions will specifically focus on the between group difference at 12 weeks [60, 61]. Differences in the primary and secondary outcome measures between the two groups will be compared. Continuously scaled outcome measures will be analysed using the analysis of covariance (ANCOVA) with baseline scores and intervention group entered as independent variables [62, 63]. Dichotomous outcome measures (e.g. frequency of adverse events, frequency of co‐interventions and dichotomised GROC) will be compared using relative risk, risk difference and number needed to treat. Intervention adherence will be compared using independent group *t*‐tests. For all analyses, both 95% confidence intervals and *p*‐values will be generated where appropriate.

A sensitivity analysis will be conducted to estimate treatment effects on the primary outcome. We will assess the robustness of the results from our analyses using the following conditions: (i) complete case analysis—only analyse participants who provide outcome data and (ii) last observation carried forward. A sensitivity analysis will also be undertaken to estimate treatment effects on the primary outcome assuming full adherence (per‐protocol analysis) [64]. Full adherence will be defined as participants reporting wearing the shoe inserts for an average of at least 35 h per week.

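### Section 2.12 schedules the primary pain score at baseline and week 12 only, which conflicts with the abstract and reduces the planned last-observation-carried-forward analysis to baseline carried forward

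*Protocol article*

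**What the plan says.** Three places in the protocol article bear on when the walking-pain score is collected.

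- **Section 2.12, Outcome measures.** "The primary outcome will be measured prior to allocation at baseline and at 12 weeks (the primary endpoint". The next sentence gives the secondary outcomes a different schedule: "All secondary outcomes unless stated otherwise will be measured prior to allocation at baseline and at 4, 8 and 12 weeks". It then refers to Table 1, whose content is not reproduced in the text at hand.
- **Abstract, Methods.** "Outcome measures will be obtained at baseline, 4, 8 and 12 weeks; the primary endpoint for assessing efficacy being 12 weeks". The sentence after it names walking pain as the primary outcome.
- **Section 2.20, Statistical analysis.** "A sensitivity analysis will be conducted to estimate treatment effects on the primary outcome". Two missing-data conditions follow: complete cases, where the plan will "only analyse participants who provide outcome data and (ii) last observation carried forward". The paragraph on the primary outcome also explains the focus on week 12 in these terms: "To avoid over‐testing and to minimise the risk of type I error associated with serial measurements".

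Section 2.20 lists the multiple-imputation predictors as allocated group, age, sex and baseline scores. Section 2.9 sends online questionnaires every 4 weeks.

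**The concern.** Carrying the last observation forward presupposes that some participants have a score after baseline but before week 12. Section 2.12 provides none for the primary outcome. Either the schedule is misworded and pain is in fact collected every 4 weeks, or the analysis is misnamed and is really baseline carried forward. The two make different assumptions: one takes the most recent pain score on treatment as the week-12 score, the other takes pain to be unchanged in everyone lost.

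What is at stake is one of the two missing-data checks on the trial's primary outcome. If the point stays open until the data are seen, the method could be settled or relabelled afterwards. It also decides whether earlier pain scores exist that could inform the imputation.

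**Working it through.** **1. The plan's own figure.** Inputs from section 2.19: difference 1.1, SD 2.2, power 80%, alpha 0.05 (taken as two-sided, which is not stated), loss 10%.

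n per arm = 2 × (1.960 + 0.842)² × (2.2/1.1)² = 2 × 7.85 × 4 = 62.8, so 63. The total is 126, and 126/0.90 = 140. The t-test version gives 64 per arm, 128 in total; 128 × 1.10 = 140.8 and 128/0.90 = 142.2. The stated 140 is reproduced, so 1.1 points and 10% loss are used below as the design values.

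**2. The passages side by side.**

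| Place | Pain score at weeks 4 and 8? |
|---|---|
| Section 2.12 | No, in explicit contrast with the secondary outcomes |
| Abstract | Yes on its natural reading, though it speaks of outcome measures collectively |
| Section 2.20, carried-forward analysis | Presupposed if the method is to differ from carrying baseline |
| Section 2.20, remark on serial measurements | Suggested, not stated |
| Table 1 | Not shown |

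**3. What can be carried.** Section 2.7 completes baseline assessments before allocation, so every randomised participant should have a baseline score. Under section 2.12 the next score is week 12. For anyone missing week 12, the last observation is therefore always baseline. This follows from sections 2.12 and 2.20 alone, without the abstract.

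**4. Size with equal loss.** Let Δ be the true week-12 difference, m the share lost (equal in both arms, unrelated to outcome), and f the share of Δ present in the carried scores.

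Expected difference = (1 − m)Δ + m·f·Δ

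- Baseline carried (f = 0): 0.90 × 1.1 = 0.99
- Week-4 or week-8 score carried, f = 0.5 (assumed): 0.99 + 0.10 × 0.5 × 1.1 = 1.045
- The same, f = 0.8 (assumed): 0.99 + 0.10 × 0.8 × 1.1 = 1.078

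The shift under baseline carried forward is 0.11 points, or 10% of the target difference. For scale, with 70 per arm and an assumed baseline-to-week-12 correlation of 0.40, the ANCOVA standard error is about 2.2 × √(2/70) × √(1 − 0.40²) = 0.34.

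**5. Size with unequal loss.** Assumed mean improvements are 2.1 (orthoses) and 1.0 (sham), a difference of 1.1.

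| Loss, orthoses / sham | Baseline carried | 80% of improvement carried |
|---|---|---|
| 5% / 15% | 2.1 × 0.95 − 1.0 × 0.85 = 1.145 | 2.1 × 0.99 − 1.0 × 0.97 = 1.109 |
| 15% / 5% | 2.1 × 0.85 − 1.0 × 0.95 = 0.835 | 2.1 × 0.97 − 1.0 × 0.99 = 1.047 |

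Carrying baseline can move the estimate either way, and in both cases moves it further than carrying an interim score would.

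**The case against.** **The score may already be collected at weeks 4 and 8.** Table 1 is cited as the schedule and is not shown. The abstract and section 2.20 both lean towards repeated measurement, so one misworded sentence is at least as likely as a missing measurement. This stands: a reader might infer that pain is left out of the interim questionnaires, and the documents do not establish that. The text would still need reconciling.

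**The conflict with the abstract is soft.** The abstract is equally loose about the global rating of change, which section 2.14.2 takes at 12 weeks only, and the remark on serial measurements could refer to the secondary outcomes. This also stands, but the mismatch between sections 2.12 and 2.20 does not depend on either.

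**The analysis can be run.** A reader might infer that last observation carried forward is impossible under section 2.12. It is not: baseline is an observation, and carrying it gives a crude no-improvement scenario. The fault is in the name and the unstated assumption. Measuring a primary outcome only at baseline and its endpoint is also a legitimate design.

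**A spurious treatment effect does not follow.** Simulation with no true effect can give baseline carried forward a false difference of about −0.14 points. That requires assumed losses of 17% (sham) against 5% (orthoses) and dropout driven by pain, neither of which is in the documents. Carrying week-8 scores is also biased there, by about −0.07 to −0.09, so the net penalty is roughly 0.07 points.

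**Interim scores would not by themselves improve the imputation.** The predictor list in section 2.20 has no place for them. This stands, and the fix has to address it.

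**Conclusion.** The point holds as an inconsistency of moderate severity. Section 2.12 as written and the carried-forward analysis in section 2.20 do not fit together, and the abstract suggests a different schedule. If section 2.12 is operative, that analysis is baseline carried forward. On the plan's 1.1 points and 10% loss it would on average return 0.99, provided loss is equal between arms and unrelated to outcome. Under the assumed unequal losses above, the range is 0.84 to 1.15.

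The week-12 ANCOVA, the complete-case analysis and the sample size of 140 are unaffected, and the multiple imputation can be carried out as listed. The documents do not support the stronger conclusions that the primary analysis is compromised or that the interim scores are certainly missing. Table 1 may show which schedule is in use.

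**What to change.** State one schedule for the walking-pain score, identically in the abstract, section 2.12 and Table 1, and settle it before any unblinded analysis.

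- **If the score is, or can be, on the existing week-4 and week-8 questionnaires:** say so in section 2.12, keep 12 weeks as the sole primary endpoint, and add the week-4 and week-8 pain scores to the imputation predictors in section 2.20. Last observation carried forward then means what its name says.
- **If it is collected only at baseline and week 12:** rename the analysis baseline carried forward and state its no-change assumption, or replace it with another missing-data sensitivity analysis.

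If the score is already collected, the cost is a wording correction and a longer predictor list. If it has to be added, the cost is one item at two existing online contacts, with no extra visits. Section 3.1 puts the start of recruitment in September 2023 and the end of follow-up at December 2024, so participants already past those timepoints would lack the interim scores. Late in follow-up, renaming or replacing the analysis is the more practical course.
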